### Participants

The study will be solely undertaken at St Vincent’s Public Hospital. The care providers involved with the study will include plastics and reconstructive surgery consultants and registrars. A total of 500 patients will be recruited and divided evenly into the two treatment groups.

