### Inclusion and Exclusion Criteria

Inclusion criteria for the study include (1) greater than or equal to 18 years of age; (2) able to give informed consent and willingness to participate in follow-up; and (3) undergoing any plastic surgery procedure involving excision of skin lesions. Exclusion criteria include those requiring re-excision through the original wound and undergoing injectable corticosteroid therapy into the scar.

The patients will be randomly allocated to receive either the deckled incision or the straight line incision for their surgery. In patients with multiple (two or more) separate lesions requiring separate incisions, each lesion will be randomly allocated to receive either the deckled or straight line incision. Only the treating surgeon will be aware of which incision was used and the patient will be blinded to the type of incision. The surgeon will document in the operation note the number and site of lesions, whether they were deckled or not, the precise length of the scar, and whether the procedure was carried out by a registrar or consultant.

The patient will be followed-up in the outpatient clinic. Standard post-operative care with micropore tape will be given to both groups with respect to scar minimization. The scar and compliance with standard post-operative scar reduction will be assessed at 1 week, 3 months, and 6 months post-operatively using the POSAS [5]. The 6-month cut off was chosen as scars have usually matured by 6 months to reflect their final life-long appearance and to avoid a large number of patient attrition over a longer follow-up period (Figure 1).

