### Enrolment Procedure

The participant will be enrolled into the study after the informed consent process has been completed, and the participant has met all inclusion criteria and none of the exclusion criteria. The patient’s baseline characteristics will be recorded on a pre-populated A4 sheet and scanned via email to a single email address. The patient baseline characteristics that will be recorded are age, gender, smoking, Fitzpatrick classification of skin type and ethnicity, presence of vascular co-morbidities, diabetes, use of systemic and/or oral steroids or immunosuppressant’s, previous poor scar results, site of lesions (face vs trunk vs limbs), and previous radiotherapy over the surgical site. An independent person will subsequently enter the patient data into an online database and allocate a study code, which will be documented in the patient records.

The final statistical analysis will be stratified and adjusted by the patients’ baseline characteristics to adjust for their effects on wound healing. We are particularly interested in effects of previous radiotherapy and sites of lesions (face vs trunk vs limbs) as we believe that the deckling incision will offer the most benefit in those with previous radiotherapy and in lesions on the face.

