### Randomization Procedure

Following suitability for enrolment into the study and allocation of study code, the participants will be randomized to receive either the deckled incision or the standard straight line incision in a simple fashion using a random computer number generator. This will be done in the anesthetic bay after confirmation of patient suitability by checking the medical records. The surgeon will subsequently ring an external number and the study nurse will specify what treatment the individual lesions will receive.

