### Blinding

In order to achieve allocation concealment an external third party will be used to assign the treatment group. The surgeon will document in the patient notes which incision was carried out for a specific lesion. This will be entered into the patient database by an independent third party.

The patient will be blinded to the type of incision that is done for any given lesion. However, it is impractical to blind the individual surgeon. In addition, the outcome adjudicators will also be blinded to the incision used. The data collectors and analysis will be centralized and remain independent of the outcome adjudicators at all times. Medical record numbers will also be recorded to enable tracking of progress over time.

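### The operator is not declared before the allocation is heard, so incision type may become confounded with operator grade (consultant or registrar)

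*Protocol article*

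**What the plan says.** Participants: "The care providers involved with the study will include plastics and reconstructive surgery consultants and registrars". No rule is given for which grade takes which case.

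Randomization Procedure: allocation is made "in a simple fashion using a random computer number generator", with no mention of stratifying by operator. On place and timing: "This will be done in the anesthetic bay after confirmation of patient suitability by checking the medical records". Then: "The surgeon will subsequently ring an external number and the study nurse will specify what treatment the individual lesions will receive".

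Blinding: patients and outcome adjudicators are blinded. On the surgeon: "However, it is impractical to blind the individual surgeon".

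Inclusion and Exclusion Criteria: the surgeon's operation note holds the number and site of the lesions, whether each was deckled, and "the precise length of the scar, and whether the procedure was carried out by a registrar or consultant". This is the only place where operator grade appears.

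Enrolment Procedure: the list of enrolment variables opens "The patient baseline characteristics that will be recorded are age, gender, smoking, Fitzpatrick classification of skin type and ethnicity" and continues with patient and lesion factors only. The stated adjustment is: "The final statistical analysis will be stratified and adjusted by the patients’ baseline characteristics to adjust for their effects on wound healing".

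**The concern.** Randomization balances what is settled before allocation. It does not protect a factor that can still be chosen once the arm is known. Here the article gives the order of events: an unblinded surgeon hears the incision for each lesion, the procedure follows, and the grade of the person who did it is noted afterwards. A team could, knowingly or not, give one type of incision to the consultant and the other to the registrar. Because allocation is by lesion, this could even happen within one patient's session.

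If it did, a difference in scar score could partly reflect who closed the wound. Blinding patients and assessors would not help, because a better closure is a real difference in the scar. Nor could the analysis recover afterwards. Operation-note grade may itself be a consequence of allocation, so adjusting for it is unreliable, and an intended operator who was never logged cannot be reconstructed.

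**Working it through.** **1. Order of events in the article**

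| Step | Section | Is the arm known? |
|---|---|---|
| Patient and lesion characteristics recorded | Enrolment Procedure | No |
| Randomization in the anesthetic bay; surgeon rings | Randomization Procedure | Becomes known |
| Excision and closure by consultant or registrar | Participants | Yes |
| Grade entered in the operation note | Inclusion and Exclusion Criteria | Yes |

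No step before the call names the operator.

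**2. The plan's own figure, as a yardstick**

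Statistical Consideration gives 250 per group, a 5% type I error and 90% power. The article gives no effect size or SD, so 250 cannot be reproduced; it can only be turned into a detectable difference. I assume a two-sided test.

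- SE of a standardized mean difference = √(2/250) = 0.0894.
- Detectable difference = (1.960 + 1.282) × 0.0894 = 0.290 SD.
- With 225 analysed per group (250 less 10% attrition): SE = √(2/225) = 0.0943, and the detectable difference is 0.306 SD.

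**3. Bias if grade differs by arm**

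Bias = (difference between arms in consultant share) × (consultant–registrar difference in scar score, in SD). The article gives neither factor, so both are assumed. With no true incision effect, the two-sided rejection rate is 1 − Φ(1.960 − t) + Φ(−1.960 − t), where t = bias/SE. At 250 per group:

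| Skill gap (assumed) | Share difference (assumed) | Bias | Type I error |
|---|---|---|---|
| any | 0 points | 0 | 5.0% |
| 0.3 SD | 10 points | 0.03 SD | 6.3% |
| 0.2 SD | 20 points | 0.04 SD | 7.3% |
| 0.3 SD | 20 points | 0.06 SD | 10.3% |
| 0.5 SD | 20 points | 0.10 SD | 20.1% |

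Worked line: 0.20 × 0.5 = 0.10; t = 0.10/0.0894 = 1.118; 1 − Φ(0.842) + Φ(−3.078) = 0.201. Against the yardstick, 0.10/0.290 is about a third of the detectable difference. With 225 per group the 0.03 SD and 0.10 SD rows become 6.2% and 18.6%.

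The direction is not determined. If consultants take more of the straight closures, the same bias would hide a benefit of deckling instead of creating one.

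**4. What a later look at operation-note grade could show**

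Suppose the operator is independent of the arm and half the procedures are done by consultants (assumed). The SE of the share difference is then √(0.25 × 2/250) = 0.0447, and the 95% chance range is ±1.96 × 0.0447, about ±9 points. An imbalance within that range could be chance or choice. A much larger one would point to choice, but without a declared operator nobody could say which cases had moved.

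**The case against.** The strongest case against has four parts.

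- **The operator may already be in place.** A surgeon makes the call, and the article says that only the treating surgeon will know the incision. Read naturally, the caller is the operator, and a handover would bring a second surgeon into the secret. This has some force. However, the same section has the surgeon document whether a registrar or a consultant did the procedure, so the person who calls and documents need not be the person who operates. No sentence ties the two together.
- **The article is condensed.** Theatre staffing and the call script may be in the full protocol. That is fair as to detail, but the article does set out who calls, when, who answers and where grade is recorded. The point concerns that stated sequence.
- **There is little motive to swap.** The article says the deckled incision is already in regular use in the department and is easy to learn. If so, the risk is smaller. But ease of deckling is not the same as equal closure skill across grades, and the article also states an expectation that deckling will be superior.
- **Every bias figure is assumed.** This stands in full.

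Two stronger readings are tempting. A reader might infer that incision type *is* confounded with operator skill. The document does not support that: it nowhere says that operators are chosen or changed by arm, and recording grade late does not in itself create confounding. A reader might also infer that the recorded grade will go unused. The article says only that patient characteristics will be adjusted for. It does not rule out other uses, and the analysis plan is not shown.

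**Conclusion.** The point holds as a gap in conduct, not as a demonstrated bias. The described sequence leaves the choice of operator open after an unblinded surgeon knows the arm, and the only record of grade comes later. Grade may therefore become associated with incision type, with no pre-allocation record against which to check.

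The size is unknown. It is zero if the operator does not depend on the arm, negligible at 0.03 SD (about 6% type I error), and material at 0.10 SD (about 20%). These figures rest on assumed skill gaps and share differences, a two-sided 5% test, 250 analysed per group and a normal approximation. The change is worth making because it costs so little, not because the larger figures are likely.

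**What to change.** 1. **Randomization Procedure.** On the existing call, have the surgeon state the intended operator and grade for each lesion before the study nurse reads out the allocation. The nurse logs it at that moment. Any later change of operator is recorded with its reason.
2. **Enrolment Procedure.** Add this pre-declared grade to the adjustment factors. It is a new field, distinct from the operation-note grade, which should be kept so that the two can be compared by arm.

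The declared grade is a true baseline covariate, so adjusting for it deals with chance imbalance. It does not undo a swap. What discourages swaps and makes them visible is the log of changes. If the declared operator performs the procedure under either arm, the expected share difference and the bias are both zero, and the type I error is 5%.

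Cost: one question on a call that already takes place, one extra logged item, and slightly less freedom to swap operators in theatre.

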**Figure 1 figure1:**
[figure not shown]
Study flow chart.

### Investigation Plan

The intervention plan is shown in Table 1.

**Table 1 table1:** Intervention plan.

List interventions	Enrolment visit	1 Week	3 Months	6 Months
Informed consent	✓			
Inclusion/exclusion criteria	✓			
Medical history	✓			
Patient and observer scar assessment scale (POSAS)		✓	✓	✓
Adverse event and serious adverse event assessment		✓	✓	✓

The follow-up will be done in the outpatient setting. The POSAS requires at least three independent assessors to achieve a valid result and this will be done by a combination of medical and nursing staff. The results will be recorded in real-time on a tablet (iPAD), which has been pre-populated with the patient demographics and the unique study code identifier that can be cross referenced with the medical records. The data is automatically backed up to an online database via Dropbox. Selected photographs will be taken by a digital camera for future publication purposes.

The routine standard of follow-up will vary with each individual procedure and thus the above protocol is not the standard of care. The additional costs of the procedure will be covered by the Plastics and Reconstructive Surgery Department.

### Study Procedure Risks

We anticipate minimal additional risks by undertaking the study. The deckled incision is fairly common practice among the Plastic Surgery Department and as previously illustrated in the pilot study, all other aspects of the post-operative care are standard.

### Recruitment and Screening

The patient will be recruited from outpatient and inpatient referrals and the Emergency Department at St Vincent’s Public Hospital.

### Informed Consent Process

Once the patient is identified as suitable, informed consent will be obtained to be enrolled in the study. The patient will be explained how the procedure is conducted, the expected post-operative recovery time, and the follow-up time periods. The risks and benefits of the procedure will be explained and the patient will be made aware of suitable alternatives [6].

### Enrolment Procedure

The participant will be enrolled into the study after the informed consent process has been completed, and the participant has met all inclusion criteria and none of the exclusion criteria. The patient’s baseline characteristics will be recorded on a pre-populated A4 sheet and scanned via email to a single email address. The patient baseline characteristics that will be recorded are age, gender, smoking, Fitzpatrick classification of skin type and ethnicity, presence of vascular co-morbidities, diabetes, use of systemic and/or oral steroids or immunosuppressant’s, previous poor scar results, site of lesions (face vs trunk vs limbs), and previous radiotherapy over the surgical site. An independent person will subsequently enter the patient data into an online database and allocate a study code, which will be documented in the patient records.

The final statistical analysis will be stratified and adjusted by the patients’ baseline characteristics to adjust for their effects on wound healing. We are particularly interested in effects of previous radiotherapy and sites of lesions (face vs trunk vs limbs) as we believe that the deckling incision will offer the most benefit in those with previous radiotherapy and in lesions on the face.

### Randomization Procedure

Following suitability for enrolment into the study and allocation of study code, the participants will be randomized to receive either the deckled incision or the standard straight line incision in a simple fashion using a random computer number generator. This will be done in the anesthetic bay after confirmation of patient suitability by checking the medical records. The surgeon will subsequently ring an external number and the study nurse will specify what treatment the individual lesions will receive.

### Adverse Events

An adverse event is any untoward medical occurrence that results in the following: death, is life-threatening, requires inpatient hospitalization or prolongation of existing hospitalization, persistent or significant disability and/or incapacity or congenital or birth defect, and any condition requiring medical or surgical intervention. An adverse event can therefore be any unfavorable or unintended sign, symptom, condition, and/or an observation that may or may not be related to the study treatment.

### Blinding

In order to achieve allocation concealment an external third party will be used to assign the treatment group. The surgeon will document in the patient notes which incision was carried out for a specific lesion. This will be entered into the patient database by an independent third party.

The patient will be blinded to the type of incision that is done for any given lesion. However, it is impractical to blind the individual surgeon. In addition, the outcome adjudicators will also be blinded to the incision used. The data collectors and analysis will be centralized and remain independent of the outcome adjudicators at all times. Medical record numbers will also be recorded to enable tracking of progress over time.

### Statistical Consideration

Sample size was calculated on the basis of a type I error of 5% (ie, *P* <.05) and a type II error of 10% (ie, power of 90%) with the aid of a statistician. Using formal sample size calculations we estimated a sample size of 250 patients for each treatment group. We anticipate an attrition rate of 10%, and subsequently, have increased our sample size by that amount for each treatment group.

Statistical analysis will be carried out by an external statistician. We intend to use independent two-sample *t* tests on primary endpoints and both chi-squared and independent two-sample *t* tests on secondary endpoints.

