## Methods

### Objectives

The primary objectives of the study are (1) to assess clinician opinion of scar quality using the observer component of the Patient and Observer Scar Assessment Scale (POSAS); and (2) to assess the patient’s opinion of scar quality and/or sensation using the patient component of POSAS.

The secondary objectives are (1) to assess the proportion of scars described as good by the clinician (determined by ≤5 on the overall component of the POSAS); (2) determine the number of adverse events overall and by individual components (namely dehiscence infection, keloids); and (3) calculate the percentage of the scar visible as a percentage of the total length at 1 month.

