### Design

The deckling study will be a patient-blinded, simple RCT at a single center institution. The two groups will be equally allocated on a 1:1 ratio into the control and treatment arms. There will be two groups: those that receive the deckled incision and those that receive the standard straight line incision.

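### Two primary POSAS endpoints share one 5% type I error and one 90% power, with no primary visit named and no rule on whether one or both must succeed

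*Protocol article*

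**What the plan says.** All references are to the protocol article.

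- **Objectives** lists two primary objectives: "The primary objectives of the study are (1) to assess clinician opinion of scar quality using the observer component" of POSAS, and second, the patient's opinion using the patient component.
- **Inclusion and Exclusion Criteria** says that the scar "will be assessed at 1 week, 3 months, and 6 months post-operatively using the POSAS". Table 1 repeats the three visits. The same section explains that follow-up stops at 6 months because scars have usually matured by then and because longer follow-up would lose patients.
- **Statistical Consideration** gives one error rate, "Sample size was calculated on the basis of a type I error of 5"%, together with "a type II error of 10% (ie, power of 90%) with the aid of a statistician", and arrives at "we estimated a sample size of 250 patients for each treatment group". Its second paragraph plans independent two-sample t tests for the primary endpoints, in the plural.
- **Abstract, Objective** speaks of a single primary objective that covers the clinician's and the patient's opinion.

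No section names the primary visit, says whether one or both primary endpoints must succeed, or divides or orders the 5% between them.

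**The concern.** A single type I error and a single power describe one test, or one decision rule that combines several tests. Here there are two primary endpoints and no rule to combine them, so the reader cannot tell what result would count as a positive trial.

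The two natural rules pull in opposite directions. If success on either endpoint is enough, the chance of a false positive conclusion exceeds the stated 5%. If success on both is needed, the chance of a true positive conclusion falls below the stated 90%. With the visit also open, the decisive time point could be chosen after the results are seen. At stake are the credibility of a positive claim and the meaning of the sample size.

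**Working it through.** **Inputs from the article:** type I error 5%; power 90%; 250 per group, 500 in total; 1:1 allocation; attrition 10%; two primary endpoints; three POSAS visits.

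**Assumed, because the article does not give them:** two-sided tests; the correlation between test statistics, varied over a range; 90% power for each test taken alone.

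**1. The plan's own figure.** The 250 per group can be neither reproduced nor refuted, because no difference, SD, endpoint or visit is stated for it. Solving backwards, d = (z₀.₉₇₅ + z₀.₉₀) × √(2/n):
- n = 250: (1.960 + 1.282) × √(2/250) = 0.290 SD.
- n = 225 (250 × 0.9, if 250 already includes attrition): (1.960 + 1.282) × √(2/225) = 0.306 SD.

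These are implied values, not values from the document.

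**2. Either endpoint may win, 6 months only.** Family-wise error = P(|Z₁| > 1.96 or |Z₂| > 1.96) under the null, with (Z₁, Z₂) bivariate normal. For independent tests this is 1 − 0.95² = 9.75%.

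| Assumed correlation | Family-wise error |
|---|---|
| 0 | 9.75% |
| 0.3 | 9.5% |
| 0.5 | 9.1% |
| 0.7 | 8.4% |
| 0.9 | 7.0% |

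**3. Both endpoints must win, 6 months only.** The error cannot exceed 5%, because each test must separately pass at 5%. With 90% power for each test, joint power = P(Z₁ < 1.282 and Z₂ < 1.282). For independent tests this is 0.90² = 81%.

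| Assumed correlation | Joint power |
|---|---|
| 0 | 81% |
| 0.5 | 83% |
| 0.7 | 85% |
| 0.9 | 87% |

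**4. Worst case: either endpoint at any of three visits.** Six tests at 5% give 1 − 0.95⁶ = 26.5% if independent. In a simulation with correlation 0.3 to 0.7 between the two raters and 0.5 to 0.7 between visits, the error runs from 23.0% (0.3 and 0.5) down to 17.7% (0.7 and 0.7). With one common correlation of 0.9 among all six it is 10.8%. The article does not state this analysis.

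**5. Cost of Holm.** The first step is at 2.5% two-sided (critical value 2.241). For d = 0.29, power is approximately Φ(d√(n/2) − 2.241):
- n = 250: Φ(3.242 − 2.241) = about 84%.
- n = 225: Φ(3.076 − 2.241) = about 80%.

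**The case against.** A reader might infer that both endpoints will be t-tested at all three visits, each at P<.05, so that the 5% simply fails. The document does not support that. The P<.05 appears only as a gloss on the type I error behind the sample size. The sentence on t tests names no visit, no number of tests and no threshold. A schedule of assessments is not a plan to test each one, and the scar-maturity rationale points to 6 months. The 18% to 23% is therefore a worst case under assumed correlations.

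Nor does the 5% fail unconditionally. It is exceeded only if a single significant endpoint counts as success. The abstract's wording, which takes in the clinician's and the patient's opinion together, is compatible with requiring both. It states no success rule, however, and requiring both moves the problem to power.

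It can also be said that this is a condensed article and that multiplicity procedures often sit in an analysis plan, which is not shown. That is fair for the mechanics, and this point does not rest on their absence. What remains is that the article itself sets two primary endpoints against one error rate and one power. Which outcome, at which visit, decides the trial is a design choice on which the sample size depends.

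Finally, the correlations are assumptions. Within the range shown, they change the size of the excess or of the power loss but do not remove it.

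**Conclusion.** The point holds in this limited form. With two primary endpoints, no primary visit and no either-or-both rule, the stated 5% and 90% cannot both describe the overall conclusion:

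- either may win, at 6 months: error about 7% to 9.75%;
- both must win, at 6 months: error within 5%, joint power about 81% to 87%;
- any visit may also count (worst case, not stated in the document): error about 18% to 23%.

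These sizes rest on two-sided tests, on correlations of 0 to 0.9 for the two 6-month cases and the narrower ranges given above for the third, and on 90% power for each test alone. The 0.29 SD is back-solved from 250 per group and is not a design assumption that the article declares.

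**What to change.** Name 6 months, which the article already justifies by scar maturity, as the only primary time point, and make the 1-week and 3-month scores secondary. Then choose one rule for the two endpoints, before any outcome data are seen:

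- **Fixed order.** Test observer POSAS at two-sided 5%, and patient POSAS at 5% only if the first is significant. This holds the family-wise error at 5%, leaves the power of the first test unchanged and needs no extra patients. The cost is that the patient score cannot be claimed alone if the observer score fails. The article numbers the two objectives but does not rank them, so the order has to be a deliberate decision.
- **Holm.** Either endpoint can then be claimed alone. The cost is power at the 2.5% step: for 0.29 SD, about 84% with 250 evaluable per group and about 80% with 225.

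If both endpoints are to be required instead, say so. No adjustment of the 5% is then needed, but the power must be restated for the joint requirement.

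For fixed order or Holm, the change to the text is about two sentences.

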**Methods:**

The deckling study will be a patient-blinded, simple randomized controlled trial (RCT) at a single center institution. The two groups will be equally allocated on a 1:1 ratio into the control and treatment arms. All patients greater than 18 years of age undergoing a plastic surgery procedure involving excision of skin lesions will be enrolled. Any patients requiring re-excision through the wound or undergoing injectable corticosteroid therapy will be excluded. A total of 500 patients will be enrolled. The patients will be followed-up at 1 week, 3 months, and 6 months post-operatively.

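### The calculated sample size and the enrolment target are both 250 per group, although the text says 10% was added for attrition

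*Protocol article*

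**What the plan says.** Under Statistical Consideration the protocol article sets a type I error of 5% and a power of 90%, and gives the result: "Using formal sample size calculations we estimated a sample size of 250 patients for each treatment group". The next sentence deals with losses: "We anticipate an attrition rate of 10%, and subsequently, have increased our sample size by that amount for each treatment group".

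The enrolment target appears in two other places. The Abstract (Methods) says: "A total of 500 patients will be enrolled". The Participants section says: "A total of 500 patients will be recruited and divided evenly into the two treatment groups". The Design section confirms 1:1 allocation. No total above 500 and no group size other than 250 is printed anywhere in the article.

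**The concern.** Three statements have to fit together: a calculated size, a 10% increase on it, and an enrolment target. As printed, the first and the last are the same number although an increase is said to lie between them. Either the target or the description of the 250 needs correcting.

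What is at stake is the meaning of the stated 90% power. The Study Rationale justifies the trial partly on the ground that earlier studies were underpowered. The Duration section ties the end of recruitment to reaching the required sample size, so that number should be unambiguous. If 250 evaluable patients per group are needed, a target of 500 has no allowance for the attrition that the authors themselves expect.

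**Working it through.** **Inputs from the article.** Type I error 5%, power 90%, 250 per group, attrition 10% (Statistical Consideration); 500 enrolled (Abstract; Participants); 1:1 allocation (Design); independent two-sample t test on the primary endpoints (Statistical Consideration).

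**Assumptions added here.** The test is two-sided, since sidedness is not stated. Each patient contributes one observation. Attrition is exactly 10% in each group.

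**Can the 250 be reproduced?** Not from the article, which prints no target difference or SD. A condensed article may leave these to the full protocol, so their absence is not held against it. The check therefore starts from the printed 250 and works backwards.

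**Reading A: 250 is the size before attrition.**
- Adding 10%: 250 × 1.10 = 275 per group, 550 in total.
- Allowing for 10% loss: 250 / 0.90 = 277.8, rounded up to 278 per group, 556 in total.
- The printed target is 500 = 2 × 250, which is 50 to 56 patients fewer.
- Completers if 500 are enrolled: 250 × 0.90 = 225 per group.
- Standardised difference implied by 250 per group at 90% power: d = (1.960 + 1.2816) × √(2/250) = 0.290 SD.
- Power at that difference with 225 per group: Φ(0.290 × √(225/2) − 1.960) = Φ(3.075 − 1.960) = Φ(1.115) = 86.8%.
- The noncentral t distribution gives 86.7%. A one-sided 5% test gives 87.1%.

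The power figure does not depend on knowing the true difference or SD. Under the normal approximation it depends only on the ratio of the two sizes: 3.2415 × √(225/250) = 3.075. The 0.290 SD is just a convenient way of expressing the same step.

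**Reading B: 250 already includes the increase.**
- If the size was divided by 0.90: 225 / 0.90 = 250 exactly. With 225 completers the power is 90.0%, at an implied 0.306 SD.
- If the size was multiplied by 1.10: 250 / 1.10 = 227.3, so about 227 (227 × 1.10 = 249.7). With 225 completers the power is 89.7%, at an implied 0.304 SD.

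| | Calculated per group | Enrolled per group that fits | Power with 225 completers |
|---|---|---|---|
| Reading A | 250 | 275 to 278 | about 87% |
| Reading B | 225 to 227 | 250 | 89.7% to 90.0% |

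The printed target of 250 per group fits Reading B. The printed description of 250 as the result of the calculation, with the increase mentioned afterwards, fits Reading A.

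**The case against.** The strongest defence is that the attrition sentence is in the perfect tense and may simply explain how 250 was reached. The target of 500 in two other sections agrees with that, and 225 / 0.90 gives 250 with no rounding. On that view nothing is short and the paragraph is only badly ordered. This stands as a possibility. It does not remove the problem, because the paragraph presents 250 as the output of the formal calculation and places the increase after it. A reader who takes the sentences in order arrives at 550 or more.

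A second objection is that the 87% is conditional and modest. This also stands. It holds only under Reading A and the assumptions listed above. Two other features of the article could move it: lesions within a patient are randomised separately (Inclusion and Exclusion Criteria), so patients and observations per group may differ, and the analysis is to be adjusted for baseline characteristics (Enrolment Procedure). Under the stated assumptions the loss is about 3 percentage points.

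A reader might infer something stronger: that the increase was never applied and the trial will not have its 90% power. The article does not support that. It does not say whether 250 is the number before or after attrition, and on one of the two readings the power is intact.

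**Conclusion.** The inconsistency is real and can be seen from the printed numbers alone: the calculated size and the enrolment target are identical although a 10% increase is said to separate them. Its effect on power is not established. If 250 is the size before attrition, 500 enrolled gives about 87% power (type II error about 13% instead of 10%), and the target that fits the text would be 550 to 556. If 250 is the size after attrition, the power is 90% or within half a percentage point of it, and only the wording is wrong. The sentence order favours the first reading and the enrolment target favours the second. The trial's validity is not threatened on either reading, but the basis of its size should be corrected because the text contradicts itself and the correction is cheap.

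**What to change.** Keep 500 enrolled and rewrite the paragraph from the statistician's actual calculation, in whichever of these two forms is true:

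- 250 per group was calculated for 90% power without allowance for attrition; 250 per group are enrolled, about 225 are expected to be evaluable, and the power for the same difference is about 87%. The claim of an increase is removed.
- About 225 per group was calculated for 90% power and increased to 250 per group for 10% attrition.

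The sentence should name the endpoint, difference and SD that the statistician used. The 0.29 and 0.31 SD values above are worked backwards from the sample size. They are illustrations and should not be printed as the design basis unless they match the original calculation.

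The cost is one corrected paragraph with no change to enrolment; in the first case the stated power becomes slightly less favourable. If the first case applies and the sponsor prefers to hold 90%, the price is 50 to 56 more patients.
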